### Data management

Data will be kept on a REDCap database held on a secure server at Cardiff University. Participant data will be encrypted, time-stamped and pseudoanonymised using an identification number. Only the researchers will have the information needed to translate the identification number to the participant identity.

### Analyses

The flow of participants through the trial will be presented as a Consolidated Standards of Reporting Trials diagram. Baseline demographic data will be presented for all consented and randomised participants, and patterns of attrition will be examined.

The primary analysis will be time-to-event analysis of the primary outcome (time to the first depressive episode collected at 9-month follow-up) and will use the complete case dataset. However, multiple imputation will be considered as a sensitivity analysis to examine possible dropout bias in the treatment effect estimate. Consistent with clinical practice, depression in the YP will be defined as YP depression reported by either parent/YP with a planned sensitivity check for YP report only. A Cox regression model will be used to determine the difference between trial arms, the HR and 95% CI. We will investigate whether a random effect to account for the group delivery clustering in the intervention arm needs to be included in the primary model. If the effect of the clustering is negligible, this will be excluded. Assumptions of the model (eg, constant hazard) will be checked to ensure model validity. Prespecified subgroups to be compared descriptively include those defined by baseline characteristics of the YP (eg, comorbidity) and parents (eg, depression status at randomisation). External treatment use will also be compared descriptively across study arms, and its effect will be evaluated by including this as a time-varying covariate in the Cox model.

Possible effect modification (eg, by PTO response, baseline demographic factors) will be investigated by including an arm*modifier interaction term. Mediation analyses will examine the effects of potential mediators (eg, improved problem-solving skills, improved parent-child relationship) on the primary outcome via inclusion of the mediator predictor in the primary model.

A sensitivity check will explore the effect of changes to inclusion criteria on the effectiveness of the intervention (online supplemental material 4). Only 20 participants were consented prior to the implementation of these changes, meaning their inclusion is unlikely to influence the main study findings in a substantial way.

Repeated measures analysis will be used for secondary outcomes collected at 3 months and 9 months. Linear mixed effects regression will be used to account for clustering by group delivery in the intervention arm (partial effect model) and will include baseline values as covariates where appropriate. Where the assumptions of the linear regression model are not met, transformation or categorisation will be considered. Logistic regression models will be used for binary outcomes. Main group effects and 95% CIs will be presented for all outcomes.

Qualitative data analysis will use a thematic analysis approach, a process of identifying, analysing, reporting and interpreting patterns or themes.^48^ Codes will be applied to broad themes and transcripts will be examined to identify key themes and subthemes. To ensure validity, a proportion of transcripts (approximately 20%) will be double-coded by a second qualitative researcher, and any discrepancies resolved by discussion. Thematic analysis will be supported by NVivo software.

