### Sample size

We aim to recruit 400 YP and parents/carers, based on a previous study^17^ and sample size calculations. We allow for 10% loss to follow-up based on previous studies of this population and depressed YP.^1630^,^32^ The effect size observed in the study by Garber *et al*^16^ was a HR of 0.63. We expect the effect of the intervention in this RCT to be slightly greater than this due to the addition of PTO before randomisation. We therefore define the minimum clinically important difference for this study as an HR of at least 0.60 (equivalent to an 11% difference in MDD between study arms). With a sample size of up to 400 randomised participants, we estimate statistical power as 79.9% to detect a difference of at least HR=0.60 between study arms, with an assumed 10% attrition rate at 9 months, expected event rate probabilities at follow-up of 0.327 (control) and 0.211 (intervention) based on^17^ a one-sided alpha of 0.05. A HR of 0.56 (equivalent to a 12% difference between study arms) will attain 87.0% power. A STATA V.17 programme was used for this estimation.^33^

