#### SWELL programme

YP in the SWELL intervention arm will be assigned to an online group including 6–8 YP and a therapist. The group will meet via videocall for 60 min. Table 1 outlines the sessions which target factors hypothesised to contribute to the development/maintenance of depression. These include training in cognitive-restructuring skills and techniques for modifying cognitive, problem-solving, behavioural activation, assertiveness and relaxation. Continuation sessions involve revising and consolidating learning, planning how skills could be used in response to future stressors and troubleshooting attempts to apply skills. YP are provided with a workbook to help them follow the intervention content and apply the skills. Two parent information sessions are offered.

**Table 1 T1:** Overview of Skills for adolescent WELLbeing (SWELL)

Acute session 1	'Beginnings’Psychoeducation about stress and depression, identifying personal goals and measuring your mood.	Intervention components common to each sessionSession start: Ice breaker. Home practice review (excluding session 1). Mood check-in with prompts to consider contributory internal and external factors. Session end: Participants encouraged to share positive events that occurred during the previous week. Participants were encouraged to reflect on aspects of the session they found most helpful and to provide feedback on what could be different. Home practice is set related to applying learning from the content of the session in their day-to-day lives.
Acute session 2	'Coping with stress’Identifying negative automatic thoughts and triggering events.	
Acute session 3	‘Increasing positive and balanced thinking’Increasing positive and balanced thinking, review of personal goals.	
Acute session 4	‘Examining negative thoughts and sources of beliefs’Identifying unrealistic thoughts and underlying beliefs, changing these to more realistic thoughts.	
Acute session 5	'Problem solving’Problem solving – thinking of solutions, evaluating solutions, trying out solutions and evaluating their effects.	
Acute session 6	‘Being Assertive’Assertiveness training, communication styles.	
Acute session 7	'Behavioural activation’Behavioural activation and integrating into daily life (plans for action and developing positive habits).	
Acute session 8	Relaxation and ending the weekly MeetingsRelaxation techniques, progressive relaxation, pleasant imagery, breathing exercises.	

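### The stated power makes no allowance for SWELL group clustering, and the primary Cox model may drop the group term on a data-driven judgement

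*Protocol article*

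**What the plan says.** All places are in the protocol article.

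- **SWELL programme:** young people in the intervention arm "will be assigned to an online group including 6–8 YP and a therapist". Under Trial design the comparator is usual care alone, so only one arm is grouped.
- **Sample size:** the inputs are 400 randomised, event probabilities of 0.327 and 0.211, "with an assumed 10% attrition rate at 9 months", and "a one-sided alpha of 0.05". From these, "we estimate statistical power as 79.9% to detect a difference of at least HR=0.60 between study arms", and "A HR of 0.56 (equivalent to a 12% difference between study arms) will attain 87.0% power". No ICC, group size or design effect is among the inputs.
- **Analyses, primary outcome:** the team will look into whether the Cox model needs a random effect for group delivery. Then: "If the effect of the clustering is negligible, this will be excluded". The article gives no criterion for negligible.
- **Analyses, secondary outcomes:** "Linear mixed effects regression will be used to account for clustering by group delivery in the intervention arm (partial effect model". No drop rule is attached to this term.

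**The concern.** Young people who share a therapist and a group can have correlated outcomes. Such correlation raises the variance of the SWELL arm's contribution to the log hazard ratio. A power figure that assumes independence is then too high, and a model without the group term gives a standard error that is too small.

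The nesting comes from the design and is known in advance. Letting the trial's own data decide whether to model it makes the primary analysis depend on a check with little information behind it. It also leaves the primary model open to choice after outcomes are seen. The linear mixed models for secondary outcomes get firmer protection than the primary model.

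At stake are the stated power and the width of the primary 95% confidence interval.

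**Working it through.** **1. Reproducing the stated power.** Analysed: 400 × 0.90 = 360, or 180 per arm. Expected events: control 180 × 0.327 = 58.9; SWELL 180 × 0.211 = 38.0; total 96.8. |log 0.60| = 0.511; one-sided critical value 1.645.

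- Schoenfeld: √(96.8/4) × 0.511 = 2.513; power 80.7%.
- Freedman: √96.8 × (0.40/1.60) = 2.460; power 79.3%.
- Two proportions, 180 per arm: 80.1%.

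For HR 0.56 the SWELL probability is 1 − 0.673^0.56 = 0.199, giving 94.7 events. The same three methods give 88.0%, 86.4% and 87.0%.

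The stated 79.9% and 87.0% fall inside these ranges with independent observations. The methods differ by more than a point, so arithmetic alone cannot exclude a trivial allowance (Schoenfeld with ICC 0.01 and groups of six also gives 79.9%). But the section lists no such input and its figures need none.

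**2. Adding clustering in the SWELL arm only.** Design effect DE = 1 + (m − 1) × ICC, where m is the number analysed per group. If the 200 randomised to SWELL form groups of 7, there are about 29 groups with about 6.3 analysed in each. If 7 are analysed per group, 180/7 gives about 26 groups. The ICC is an assumption throughout, and a design effect is an approximation for time-to-event data.

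Two variance forms were used:

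- Pooled: Var(log HR) = (4/96.8) × (1 + DE)/2
- Arm-specific: Var(log HR) = 1/58.9 + DE/38.0

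Worked case, m = 7 and ICC 0.05, so DE = 1.30:

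- Pooled: 0.0413 × 1.15 = 0.0475, SE 0.218; 0.511/0.218 = 2.344; power 75.8%.
- Arm-specific: 0.0170 + 1.30 × 0.0263 = 0.0512, SE 0.226; 0.511/0.226 = 2.257; power 73.0%.

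One-sided power for HR 0.60:

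| ICC (assumed) | DE, m = 6.3 to 7 | Pooled form | Arm-specific form |
|---|---|---|---|
| 0 | 1.00 | 80.7% | 79.1% |
| 0.02 | 1.11–1.12 | 79.0–78.7% | 76.9–76.6% |
| 0.05 | 1.27–1.30 | 76.3–75.8% | 73.7–73.0% |

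Within each form the loss is about 2 to 6 points.

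**3. Can the data show that clustering is negligible?** In a binary-outcome simulation (26 groups of 7, event probability 0.211), a 5% heterogeneity test detected clustering in about 9%, 25% and 58% of trials at ICC 0.02, 0.05 and 0.10. The 5% test is an assumption, because the article names none. In trials where the test missed it and the term was left out, coverage of the nominal 95% interval for the risk difference was about 94.0%, 93.2% and 91.9%.

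**4. What the two-step rule does overall.** Null Cox trials were simulated with frailty in the SWELL arm only (26 or 29 groups, 4,000 trials per cell, the same assumed test). Two-sided type I error:

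| ICC | Two-step rule | Always cluster-robust |
|---|---|---|
| 0.02 | 4.7–5.2% | 4.8–5.6% |
| 0.05 | 5.1–6.1% | 4.8–5.7% |
| 0.10 | 6.0–6.6% | 5.3–6.1% |

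Monte Carlo error is about 0.35–0.4 points per estimate, and the two approaches differ by at most about 0.7 points.

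**The case against.** The plan recognises the nesting and means to examine it. Averaged over trials, its two-step rule costs little type I error, and always modelling group gains little on that measure. Negligible could mean a small estimated variance, or no material change in the hazard ratio or its interval; under the last reading, dropping the term is almost harmless. The SAP, not shown, may define it. One-to-one catch-up sessions (Adherence) may weaken correlation within groups. With 267 recruited by June 2025 and recruitment due to end that August (Trial status), restating power will not change the design.

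Most of this stands, and it limits the severity. It does not remove the point: the article commits to an exclusion rule and to specific power figures, so neither is merely a detail left to the SAP.

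Three stronger readings are tempting but not supported:

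- A reader might infer that the primary test is seriously anti-conservative. Larger inflation comes from never modelling clustering, which is not the plan.
- A reader might infer that every secondary outcome is modelled with clustering. The article ties the term to the linear mixed models and does not mention it for the logistic models.
- A reader might add the drop from about 80% to about 70% power that follows from testing two-sided. That belongs to the choice of a one-sided alpha, a separate matter from clustering.

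**Conclusion.** The concern holds as a should-fix point. The stated 79.9% and 87.0% are powers for independent observations, not for an arm treated in groups. At an assumed ICC of 0.02–0.05 the loss for HR 0.60 is about 2 to 6 points, leaving about 77–79% at 0.02 and 73–76% at 0.05. At ICC 0.01 the loss is about one point, and at zero there is none.

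The exclusion rule rests on a judgement that about 26–29 groups and 38 SWELL events cannot support well. Its effect on two-sided type I error is modest, roughly 5–6.6% over ICC 0.02–0.10. The primary interval is somewhat too narrow in those trials where real clustering goes unseen. These sizes depend on the assumed ICC, on about 6–7 analysed per group and, for the error rates, on the assumed 5% test.

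**What to change.** 1. Delete the rule that excludes the group term.
2. State that the primary Cox model always accounts for SWELL group, either with a frailty term in the intervention arm only or with cluster-robust standard errors that treat each control young person as a cluster of one. Name one method before outcome data are examined.
3. Restate power with a design effect in the SWELL arm over an assumed ICC range such as 0.02–0.05, giving the group size used.

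The cost is wording in the protocol and SAP, a slightly wider confidence interval if the true ICC is zero, and a lower stated power. No change to recruitment is implied.

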### Outcomes and assessments

Parents and YP will complete assessments with a researcher via videocall at initial screening, at baseline and 9-month follow-up post randomisation. Self-report questionnaires will be completed at baseline, 3 months and 9 months (figure 1). We selected 9-month post randomisation to assess the primary outcome for consistency with prior studies^16^ and because this aligns with completion of the full intervention. The 3-month postrandomisation follow-up was selected to allow for measurement of potential mediators and secondary outcomes following completion of the acute intervention sessions. Table 2 shows the schedule of measures.

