
### Mediators

The logic model (figure 2) shows hypothesised mediators of change for the intervention. These include measures of cognitive change, behavioural activation, perceived coping efficacy, perceived stress and quality of the parent-child relationship indexed by warmth, conflict and openness. Mediators are either targeted by the intervention; evidence indicates they may contribute to the onset and maintenance of depression and/or index environmentally mediated intergenerational links between parent and YP depression.^1645^,^47^ Possible mediators will be measured at baseline, 3 months and 9 months post randomisation. Qualitative interviews will be conducted to explore participant perceptions of possible mechanisms of action and non-specific mediators such as perceptions of the possibility of change and the group/therapeutic alliance.^45^

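### The mediation model as written lets a mediator first measured at month 3 explain earlier episodes, so it cannot separate mediation from reverse causation

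*Protocol article*

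**What the plan says.** The Analyses section defines the primary model as a Cox regression of time to the first depressive episode, comparing arms over the 9-month follow-up. It then says mediation will examine effects of potential mediators "on the primary outcome via inclusion of the mediator predictor in the primary model". The two examples given are "improved problem-solving skills" and an improved parent-child relationship.

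The Mediators section states: "Possible mediators will be measured at baseline, 3 months and 9 months post randomisation". Outcomes and assessments gives the reason for the earlier visit: "The 3-month postrandomisation follow-up was selected to allow for measurement of potential mediators" and secondary outcomes once the acute sessions are complete. Under Primary outcome, any qualifying episode in the 9-month period counts, and the interview dates onset to the week.

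The mediation sentence gives no rule for episodes that start before the mediator is measured. The same section does plan a time-varying covariate for external treatment use.

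**The concern.** A mediator must come before the outcome it is said to transmit. If a 3-month value enters a model whose clock starts at randomisation, it is used as a predictor of episodes in the first 3 months, which preceded it. Depression can plausibly worsen dysfunctional attitudes, perceived stress, activation and family conflict. A young person who became depressed in month 2 may therefore score worse at month 3 because of the episode. The fitted coefficient then mixes the mediator's effect on depression with depression's effect on the mediator, and is pushed away from the null.

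A single added covariate also gives no estimate of the path from arm to mediator, and no indirect effect. Mechanism is an explicit purpose of the trial (Abstract, Aims, Discussion), so a consequence of depression could be reported as a driver of it.

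**Working it through.** **Inputs.** From Sample size: 400 randomised, 10% attrition (360 analysed, 180 per arm at 1:1), event probabilities by 9 months of 0.327 (control) and 0.211 (intervention), and "a one-sided alpha of 0.05". Assumption, because the article gives no hazard shape: Weibull with shape k, where k = 1 is constant hazard and the range is 0.7 to 2.

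**1. The plan's own figure.** Expected events = 180 × (0.327 + 0.211) = 96.8. Schoenfeld: √96.84 × |ln 0.60| / 2 − 1.645 = 2.513 − 1.645 = 0.869, which is 80.8% power. Freedman's formula gives 79.3%. The article says "we estimate statistical power as 79.9% to detect a difference of at least HR=0.60 between study arms". The figures agree, so these event counts are a fair basis for the rest.

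**2. Share of events before month 3.** The probability of an episode by month 3 is 1 − (1 − p)^f, with f = (3/9)^k.

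Constant hazard (f = 1/3):
- Control: 1 − 0.673^(1/3) = 0.1237; 0.1237 / 0.327 = 37.8% of control events.
- Intervention: 1 − 0.789^(1/3) = 0.0760; 0.0760 / 0.211 = 36.0% of intervention events.
- Together: 180 × (0.1237 + 0.0760) = 35.9 of 96.8 events, or 37.1%.

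| Shape k | Events before month 3 | Share | Events after month 3 |
|---|---|---|---|
| 0.7 | 48.9 | 50.5% | 47.9 |
| 1 | 35.9 | 37.1% | 60.9 |
| 1.3 | 26.2 | 27.1% | 70.6 |
| 1.5 | 21.2 | 21.9% | 75.6 |
| 2 | 12.4 | 12.8% | 84.4 |

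A 9-month value, if it were used, would follow or coincide with every episode.

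**3. Illustration of the bias.** Simulated trials had 180 per arm and the event probabilities above. A variable with no causal role was made 0.5 SD worse at month 3 in those who had already had an episode (the shift is an assumption). It was entered with arm in the Cox model from randomisation and tested at two-sided 5%.

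| Shape k | HR per SD (true value 1) | Significant |
|---|---|---|
| 0.7 | about 1.27 | about 63% |
| 1 | about 1.20 | about 44% |
| 1.5 | about 1.11 | about 19% |
| 2 | about 1.07 | about 11% |

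Restricting to follow-up after month 3 in those still episode-free gave HR 0.99 to 1.01 and 4% to 9% significant. These are small runs of 200 to 400 trials per setting, so the percentages are good to a few points.

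**4. What the illustration does not show.** Adding the variable hardly moved the arm coefficient (log HR −0.492 to −0.488). A spurious indirect effect also needs the arm to shift the mediator. With an assumed shift of 0.3 SD and a biased HR of 1.18 per SD, the product is 0.3 × ln 1.18 = 0.050, against |ln 0.60| = 0.511: roughly 10% of the total effect.

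**5. Named mediator against measured mediators.** The Mediators section lists cognitive change, behavioural activation, coping efficacy, stress and the parent-child relationship. Neither that list, Table 2 nor the instruments in the Figure 2 legend include a problem-solving measure. Problem solving appears only as session content.

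**The case against.** The strongest reply is that this is one sentence in a condensed article, and that mediator timing and the estimator usually sit in the analysis plan, which is not shown. The 3-month visit was chosen for mediators, onset is dated by week, and time-varying covariates are already planned for another purpose, so a properly timed analysis is within reach. That all stands, and it makes the repair cheap. But the sentence states a method, and followed as written that method gives a biased coefficient.

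Several stronger readings are tempting, and the article does not support them:
- **That 37% of events precede the mediator, as a fact.** The figure needs a constant hazard, which the article does not state.
- **That the trial cannot identify mechanisms.** Qualitative work on mechanisms is planned, and under constant hazard about 63% of events follow the 3-month measure.
- **That 9-month values will be used as mediators.** The article says only that they are collected.
- **That Cox coefficients with and without the mediator will be compared, which non-collapsibility would undermine.** No such comparison is stated. In simulation at these event rates, an independent covariate with HR 1.3 or 1.5 per SD changed the arm log HR by only about 1%.
- **That the mediators are largely unmeasured.** Problem-solving is one of two examples, and the other is measured. Figure 2 itself is not shown, so a mapping to a listed instrument cannot be excluded.

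**Conclusion.** The point holds for the quantitative mediation model as published: it cannot separate mediation from reverse causation for episodes that start before month 3. The affected share is about 37% of events under constant hazard and about 13% to 50% across Weibull shapes 2 to 0.7. The direction of the bias in the mediator coefficient, away from the null, does not depend on the hazard shape. Its size does, and it also depends on how far an early episode shifts the mediator, which the article does not tell us. A false indirect effect may be modest even where the coefficient is clearly biased. The primary comparison of arms is not touched. The problem-solving example is a smaller mismatch of wording between Analyses and the list of measures. The change should be made before the mediation analysis is run; if the full plan already sets a timing rule, the task is to confirm that it does this.

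**What to change.** In the analysis plan, and in any later description of the method:

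- Relate the 3-month mediator only to episodes with onset after its measurement: a month-3 landmark among young people still episode-free, using the week-of-onset data.
- Adjust for the baseline mediator and baseline depressive symptoms, both already collected.
- Do not use 9-month values as mediators of this outcome.
- Report an indirect effect from a mediation method suited to survival data, not only the mediator coefficient.
- Name the instrument for problem-solving skills, or replace the example with a measured construct.

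No new data are needed. The cost is in precision and scope. About 61 of 97 events remain under constant hazard (about 48 to 84 across the shapes above). With 61 events, even the total effect at HR 0.60 would have only √61 × 0.511 / 2 − 1.645 = 0.35, or about 64% power one-sided (about 51% two-sided). Effects in the first 3 months, which include the acute sessions, are not covered. The analysis also conditions on being episode-free at month 3, a state that the intervention itself may influence. It should therefore be labelled exploratory.

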### Trial design

This is a multisite, two-arm, parallel-group effectiveness RCT with assessors blinded to allocation. YP will be randomised 1:1 to the intervention condition (the SWELL programme plus usual care) or the usual care only condition. Given that most YP do not receive preventive interventions, usual care is the appropriate comparator. The method of randomisation will be simple-permuted-block randomisation stratified by site, with the unit of randomisation being the YP (online supplemental material 2).

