### Blinding

Blinding therapists or participants is not possible for the intervention under study. Assessors at baseline and follow-ups will be blind to the intervention arm. Participants will be reminded of the importance of assessors remaining blind to allocation as recommended,^34^ and assessors will report any instances of potential unblinding. The trial statistician will remain blinded to group allocation during analysis. It will not be possible to blind the qualitative analyst(s). It is not possible to blind YP, which could lead to reporting bias. We will mitigate this by using an interviewer-led criterion-based clinical interview to define the primary outcome and standardised prompts for questionnaires. We will also evaluate the consistency of effects for outcomes reported by different raters (YP and parents/carers).

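### Categorisation is named as a possible fallback for continuous secondary outcomes; a two-category split could cost about 36% or more of the information, and methods that keep the original scale would avoid this

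*Protocol article*

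**What the plan says.** The Analyses section of the protocol article gives the secondary outcomes measured at 3 and 9 months a repeated-measures analysis. The model is a linear mixed regression that allows for clustering by delivery group in the intervention arm and adjusts for baseline where appropriate. It continues: "Where the assumptions of the linear regression model are not met, transformation or categorisation will be considered". The next sentence is "Logistic regression models will be used for binary outcomes", and the paragraph ends with "Main group effects and 95% CIs will be presented for all outcomes".

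Three other places bear on the point:

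- The Blinding section says "The trial statistician will remain blinded to group allocation during analysis". It also plans to compare effects across raters (young person and parent) as a guard against reporting bias.
- The Sample size section allows up to 400 randomised, "with an assumed 10% attrition rate at 9 months". It gives a power figure for the primary outcome only.
- Box 3 lists the scores concerned, among them CES-D, RCADS, ARI, EQ-5D-Y and depression-free weeks. It says CES-D was chosen for consistency with the earlier trial.

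**The concern.** Whether the model assumptions hold can be judged only on the collected outcome data. If categorisation is then used, both the form of the outcome and the quantity estimated depend on that check. A two-category version has a ready analysis in the logistic model named in the next sentence, so the result would become an odds ratio.

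Three things are at stake.

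- **Precision.** Collapsing a score discards information, most of all with two categories.
- **Comparability.** A categorised CES-D is harder to set beside the earlier trial. If only one rater's RCADS or ARI were categorised, the planned comparison between raters would put an odds ratio beside a mean difference.
- **Need.** With about 180 per arm, skewed residuals do little harm to a baseline-adjusted mean difference. It is mainly the standard error that needs protection, and that can be given without changing the outcome.

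**Working it through.** **Inputs from the protocol article.** Up to 400 randomised 1:1 with 10% attrition gives 400 × 0.9 = 360 analysed, or 180 per arm. Reporting with 95% confidence intervals corresponds to a two-sided 5% level. **Assumed, not in the documents:** a standardised difference of 0.30, with a range of 0.25 to 0.35.

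**The plan's own power figure.** No power is stated for secondary outcomes. The primary figure of 79.9% (HR 0.60, one-sided 5%) was reproduced to confirm the inputs:

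- Events: 360 × (0.327 + 0.211)/2 = 96.8.
- Schoenfeld: Φ(√96.8/2 × |ln 0.60| − 1.645) = 80.8%.
- Freedman: Φ(√96.8 × 0.40/1.60 − 1.645) = 79.3%.

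These bracket the stated value. The point made here does not depend on it.

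**Two-category split, normal score.** The efficiency relative to the original scale is φ(c)²/[p(1 − p)], where p is the proportion below the cut-point c. At the median it is 0.3989²/0.25 = 0.637.

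| Split | Information kept | Lost |
|---|---|---|
| 50/50 | 0.637 | 36% |
| 33/67 | 0.593 | 41% |
| 25/75 | 0.539 | 46% |
| 20/80 | 0.490 | 51% |
| 10/90 | 0.342 | 66% |

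A median split makes 360 young people act like 360 × 0.637 = 229. A 20/80 split makes them act like 360 × 0.490 = 176.

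**More categories, normal score.** The efficiency is Σ(φᵢ − φᵢ₊₁)²/pᵢ, where φᵢ and φᵢ₊₁ are the normal densities at the lower and upper bounds of category i and pᵢ is its probability. Equal-sized categories give 0.793 for three (21% lost), 0.861 for four (14%) and 0.897 for five (10%).

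**Non-normal scores, median split against the raw mean.**

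- t with 10 df: 0.757 (24% lost).
- t with 5 df: 0.961 (4% lost).
- t with 3 df: 1.62 (no loss; the split is more efficient).
- Log-normal with log-SD 0.8: 0.892 (11% lost). Against an analysis on the log scale, the efficiency is again 0.637 (36% lost).

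**Power.** The formula is Φ(d√(n/2) − 1.96), with n the effective number per arm. For d = 0.30:

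- Original scale, n = 180: Φ(2.846 − 1.96) = 81%.
- Median split, n = 180 × 0.637 = 114.6: Φ(2.271 − 1.96) = 62%.
- 25/75 split, n = 180 × 0.539 = 97.0: Φ(2.090 − 1.96) = 55%.

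| Difference (SD) | Original scale | Median split | 25/75 split |
|---|---|---|---|
| 0.25 | 66% | 47% | 41% |
| 0.30 | 81% | 62% | 55% |
| 0.35 | 91% | 75% | 68% |

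These powers assume a near-normal score and ignore baseline adjustment and clustering in every column.

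**The case against.** The planned analysis is already the preferred one, a linear mixed model on the score itself. The fallback is only to be considered, transformation is listed first, and nothing commits the trial to a two-category split. Triggers, the order of fallbacks and cut-points normally belong in the statistical analysis plan, which is not shown. All of this stands, and the absence of those details is not held against the article. What remains is that the article itself names categorisation as a remedy.

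A reader might infer that any categorisation discards a third or more of the information. The documents do not support that. The figure needs two categories and a near-normal score, whereas the fallback applies only when assumptions fail. The losses above for several categories or heavy tails are smaller, and one case shows none.

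A reader might also infer that cut-points will be picked after seeing the results. The text fixes no such thing, established cut-offs are equally compatible with it, and the statistician is to be blind to allocation. That safeguard is real but incomplete. Delivery groups exist only in the intervention arm, so fitting the clustering term tends to show which arm is which.

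Finally, the trigger is wider than non-normal residuals. Robust standard errors do not model a spike at the end of a scale. With expected episode probabilities of 0.327 and 0.211, many values of depression-free weeks may sit at the maximum. That is a fair argument for an ordinal model, which keeps the observed ordering and needs no chosen cut-point. It is a weaker argument for collapsing the score.

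**Conclusion.** The point holds as a minor one. Categorisation is an inferior fallback that is easily replaced. If it took the form of a two-category split of a near-normal score, it would lose about 36% of the information at best and more at uneven splits, and would change a mean difference into an odds ratio. The fall in power from about 81% to 62% rests on the assumed 0.30 SD, a median split, normality and 180 per arm. The relative efficiencies do not depend on the assumed difference.

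Data-driven choice of a cut-point is a residual possibility, not something the plan provides for. Transformation is a trade-off between fit and interpretability, not an error. The primary Cox analysis and its stated power are unaffected.

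**What to change.** Replace categorisation as the fallback with the following:

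- Keep each score on its original scale and report the same baseline-adjusted mean difference with robust (sandwich) or cluster-bootstrap 95% confidence intervals.
- For strongly bounded or spiked scores, use a proportional-odds mixed model.
- Report categorised results only as supplementary analyses, at cut-offs fixed in advance, for example CES-D of 16 or more, which Box 1 already uses for eligibility.
- Transformation may stay as an option.

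The cost is one sentence and a little more programming. There is no effect on recruitment or data collection. If the statistical analysis plan already says this, the sponsor need only confirm it.
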